## Abstract

**Introduction:**

Knee osteoarthritis (OA) causes pain, reduced function and disability and may require total knee replacement (TKR). Although TKR is effective, up to 20% of patients remain dissatisfied, partly due to poor preoperative function and unrealistic expectations. Long waiting times for surgery may worsen patients’ function, yet preoperative physiotherapy is rarely offered. Prehabilitation—exercise and education before surgery—could improve postoperative recovery, but current evidence is limited. This trial investigates whether adding prehabilitation to standard care before TKR improves postoperative patient-reported joint awareness, enablement and knee function.

**Methods and analysis:**

This multicentre, randomised controlled parallel-group trial is planned to be conducted within two specialised orthopaedic outpatient rehabilitation units in the southeast healthcare region of Sweden. Eligible patients (40–85 years, awaiting unilateral TKR) are randomised 1:1, stratified by age (≤67, >67 years), to either 8 weeks of prehabilitation—comprising two times per week supervised exercise therapy (strength, range of motion and balance) and education—in addition to standard care, or to standard care alone. Standard care consists of self-care, a single standardised preoperative education session and standardised postoperative rehabilitation. Assessments are conducted at baseline, post-intervention, 1 week pre-surgery and 6, 12 and 52 weeks post-surgery. A total of 110 patients will be recruited to the trial. Primary outcomes are joint awareness (Forgotten Joint Score-12) and patient enablement (modified Patient Enablement Instrument-2). Secondary outcomes are patient satisfaction (5-category Likert scale), the Knee injury and Osteoarthritis Outcome Score, the EuroQol 5 Dimension 3 Level questionnaire, the International Physical Activity Questionnaire—short form, objective function and accelerometer-based physical activity. Analyses will follow intention-to-treat and per-protocol principles. Between-group and within-group differences will be tested using t-tests or non-parametric equivalents, and linear mixed models or generalised linear models. Multiple linear regression and logistic regression will be used to analyse predictor variables for the primary outcomes. Sensitivity analyses will be performed to quantify the magnitude of missing data from patients lost to follow-up.

**Ethics and dissemination:**

The trial has received ethical approval from the Swedish Ethical Review Authority (reg. no.2023-05120-01) and complies with the Declaration of Helsinki. Signed informed consent is collected for all patients before entering the trial. Results will be submitted for publication in a peer-reviewed journal and presented at international/national conferences. The findings may improve future clinical guidelines and care pathways for patients undergoing TKR.

**Trial registration number:**

NCT06290336.

STRENGTHS AND LIMITATIONS OF THIS STUDYThe concealed, stratified randomisation reduces the risk of allocation bias.Supervision of exercise therapy ensures adequate intervention delivery and allows for easy monitoring of exercise technique, dosage and progression.Blinded assessors of objective outcomes reduce the risk of detection bias.The multicentre design promotes generalisation of trial results but increases risk of lower internal validity.Variation in waiting times for surgery between patients presents challenges for the statistical analysis.

## Introduction

 Osteoarthritis (OA) is a condition that affects the entire joint, with the knee being particularly vulnerable.^1^ The disease typically progresses over time, but symptoms such as pain, swelling, stiffness and reduced range of motion (ROM) can fluctuate. OA can result in disability, challenges with daily activities (eg, walking) and significant patient suffering.^1^ First-line treatment is non-surgical and includes patient education, activity modification, exercise therapy and pain management strategies.^2^,^4^ When these approaches are no longer sufficient, patients are often referred for assessment for joint replacement surgery.^5 6^ Total knee replacement (TKR) is the most common surgical intervention for knee OA, with approximately 19 000 procedures performed annually in Sweden.^7^ While TKR is generally a successful treatment, around 15–20% of patients report dissatisfaction 1–3 years after surgery.^7^,^9^ Reasons for dissatisfaction are multifactorial, including surgical complications, poor preoperative knee function and unrealistic expectations regarding rehabilitation and outcomes.^810^,^14^ Dissatisfaction with the surgery result is likely to indicate higher joint awareness in everyday life situations.^15 16^

In Sweden, the total waiting time, from primary care referral to orthopaedic consultation and subsequent surgery, can extend up to 12–24 months.^17^ Participation in exercise and physical activity tends to decline after first-line treatment,^18^ and this tendency may accelerate while awaiting surgery. Currently, routine physiotherapy management is rarely offered during this period, and prolonged waiting times may further reduce participation in exercise and physical activity, with subsequent loss of leg muscle strength and volume, and reduced ROM. This contributes to the deterioration of knee function, and these are factors associated with poorer outcomes after TKR.^810^,^12 19 20^ This supports the rationale for the hypothesis that improving knee function, physical activity and patient knowledge about OA and TKR before surgery, referred to as prehabilitation, may enhance postoperative results and bridge the gap between the end of first-line treatment and surgery. While exercise and education are cornerstones in both first-line treatment and prehabilitation, the aim of prehabilitation differs from that of first-line treatment. Prehabilitation aims to prepare patients for the upcoming TKR and optimise postoperative recovery, increase patients’ enablement and self-efficacy and reduce unnecessary healthcare use. However, evidence supporting prehabilitation to enhance postoperative recovery is limited and inconsistent and is largely based on low-quality, heterogeneous studies with insufficient description of interventions, control groups, progression models and adherence.^21^,^24^

A better understanding of how prehabilitation affects postoperative outcomes after TKR is needed. This trial aims to contribute to existing knowledge by investigating the combined effect of preoperative exercise therapy and patient education on postoperative outcomes, as these interventions are often studied separately in previous research. The trial also examines the impact of prehabilitation on postoperative patient-reported joint awareness and enablement, which has rarely been assessed. Additionally, objective measurement of physical activity using the activPAL accelerometer preoperatively and postoperatively provides novel insights into physical activity patterns in this population.

The aim of this trial is to investigate the effect of adding prehabilitation to standard care before TKR, compared with standard care alone, focusing on (1) patient-reported joint awareness 1 year after TKR, and (2) patient enablement and objectively measured knee function 6 weeks after TKR.

## Methods and analysis

### Trial design

The PRe-Operative exercise Therapy and Education before total Knee replacemenT (PROTEKT) trial is a multicentre parallel-group randomised controlled trial (RCT) planned to be conducted within two specialised orthopaedic outpatient rehabilitation units in the southeast healthcare region of Sweden, a region with both urban and rural patient catchment areas. This protocol is reported in accordance with the Standard Protocol Items: Recommendations for Interventional Trials (SPIRIT)^25^ and the Template for Intervention Description and Replication (TIDieR) checklist.^26^ Results will be reported in accordance with the Consolidated Standards of Reporting Trials (CONSORT) guidelines.^27^

### Patient recruitment and inclusion/exclusion criteria

Participating centres contribute to patient recruitment using a stepwise approach, with one centre initiating recruitment first and the other following in the second stage. All patients referred to an orthopaedic surgeon at the participating hospitals for assessment of the need for TKR are screened for eligibility and receive written information about the trial by post from an administrator before the appointment. Eligible patients (table 1) receive additional oral information and are invited to participate in the trial by a nurse involved in the appointment. The nurse obtains signed informed consent (online supplemental file 1) and delivers it to the trial coordinator (lead author). Time for consideration is offered if needed. An appointment for baseline measures and randomisation is scheduled by the trial coordinator. A visual representation of the trial timeline is shown in figure 1.

**Table 1 T1:** Inclusion and exclusion criteria

Inclusion criteria	Exclusion criteria
40–85 years at the time of surgery decision	Previous knee replacement in the other knee
Awaiting primary unilateral total knee replacement	Other reason than knee OA as the primary reason for surgery
Knee OA being the primary reason for surgery	Impaired cognitive function
Reside within 60 min travel time to the site of the intervention	Not fluent in written and spoken Swedish
	Chronic illness or disability, etc hindering full participation in the intervention

OA, osteoarthritis.

**Figure 1 F1:**
[figure not shown]
Trial timeline. PROMs, patient-reported outcome measures.

### Randomisation

Patients are randomised using opaque, concealed envelopes and stratified by age (≤67 years, >67 years) with a 1:1 allocation ratio, based on computer-generated random number sequences, into the intervention group, comprising prehabilitation in addition to standard care (SC+P), or the control group, consisting of standard care only (SC). The computer-generated random number envelope sequences were created by a person not otherwise involved in the trial. Allocation is performed by the trial coordinator immediately after the baseline assessment. The trial coordinator did not have access to the randomisation lists before allocation.

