### Prehabilitation

Prehabilitation consists of 8 weeks of on-site, supervised and individualised exercise therapy together with patient education. It is delivered in a group format two times per week, at a fixed time in the afternoon (approximately 1 hour per session), by physiotherapists with experience in the rehabilitation of OA and TKR.

After the 8-week intervention, patients are advised to continue the exercise therapy either in supervised sessions or unsupervised at a location of their choice until the surgery date. Patients who choose to continue with unsupervised exercise therapy have check-ins scheduled by phone or video conference every other week with the physiotherapist in charge of the intervention to discuss exercise progression and adjustments.

Physiotherapists at the participating clinics are trained in the intervention’s content and structure two times before enrolling patients. They work with the trial coordinator to review these materials, and monthly meetings are held to monitor sessions, ensure treatment fidelity and address any issues.

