### Data collection and blinding

A questionnaire covering patient demographics, lifestyle behaviours, expectations and PROMs is mailed to patients, completed and brought to the baseline assessment, where objective function measures are conducted. At the baseline assessment, a triaxial accelerometer (activPAL) is attached to the front of the thigh of the affected leg and worn 24 hours a day for 7 days. The accelerometer is then returned to the trial coordinator using a pre-paid reply envelope.

Follow-up assessments are conducted immediately after the 8-week intervention and at 6, 12 and 52 weeks post-surgery. Waiting times for surgery will vary between patients, and if more than 4 weeks elapse between the post-intervention follow-up and surgery, an additional follow-up assessment will be scheduled approximately 1 week before surgery.

PROMs are collected at every follow-up assessment. Measures of objective function are conducted at the 8-week follow-up, 1 week before surgery and 6 weeks after surgery. The activPAL accelerometer is worn 24 hours a day for 7 days immediately after the 8-week follow-up and at the 12-week and 52-week postoperative follow-up assessments.

Outcome data are collected locally at each participating centre. All PROMs in the trial are administered via paper surveys. Measures of objective function are assessed by a physiotherapist blinded to group allocation. Physiotherapists performing these assessments are trained on two occasions before participating in the trial, during which pilot measurements of objective outcome measures are conducted under the supervision of the trial coordinator. The assessors also participate in monthly meetings with the trial coordinator throughout the trial to address potential issues.

Patients are not blinded to group allocation but are not informed of the trial hypothesis until data collection is complete. An overview of the trial timeline and data collection is provided in figure 1 and table 3.

**Table 3 T3:** Data collection/outcome measures

Data collection time points	Baseline	8-week follow-up	1-week preop follow-up (if necessary)	6-week postop follow-up	12-week postop follow-up	52-week postop follow-up
Demographics, lifestyle behaviours, expectations, etc	X					
PROMs						
FJS-12	X	X	X	X	X	**X**
Satisfaction						X
Mod-PEI-2	X	X	X	**X**	X	X
KOOS	X	X	X	X	X	X
IPAQ-sf	X	X	X	X	X	X
EQ5D-3L	X	X	X	X	X	X
Objective function						
Isometric quadriceps strength	X	X	X	**X**		
Active knee ROM	X	X	X	**X**		

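### Randomisation is stratified by age only, so chance imbalance between the two centres is not controlled, and the stated between-group tests include neither age stratum nor centre

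*Protocol article*

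**What the plan says.** The Randomisation section describes opaque envelopes, "stratified by age (≤67 years, >67 years) with a 1:1 allocation ratio, based on computer-generated random number sequences". The abstract repeats the scheme: patients "are randomised 1:1, stratified by age (≤67, >67 years". Age is the only factor named in either place, and the article does not mention separate sequences per centre or blocks.

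The Trial design section says the trial is "planned to be conducted within two specialised orthopaedic outpatient rehabilitation units in the southeast healthcare region of Sweden". The recruitment section has the centres contributing "using a stepwise approach, with one centre initiating recruitment first and the other following in the second stage". The Prehabilitation section describes on-site group sessions and adds: "Physiotherapists at the participating clinics are trained in the intervention’s content and structure two times before enrolling patients". The Data collection and blinding section states: "Outcome data are collected locally at each participating centre".

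The Analysis plan assigns independent-samples t-tests or non-parametric tests to the differences between groups at each follow-up. Mixed or generalised linear models are given to longitudinal change within groups, and multiple or logistic regression to predictors of the primary outcomes. Adjustment is conditional and covers intervention delivery and adherence, duration of participation, surgical procedures and postoperative physiotherapy. Centre and age stratum are not on that list. The strengths and limitations box concedes: "The multicentre design promotes generalisation of trial results but increases risk of lower internal validity".

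**The concern.** In a two-centre trial with local delivery, centre is a natural stratification factor. Surgery, inpatient instruction and the people who run the programme can all differ by site. Sequences that ignore centre may balance the arms overall and within age groups, but nothing holds the ratio near 1:1 within each centre. If one arm happens to receive more patients from a centre with better or worse results, the treatment contrast moves with it. An unadjusted test cannot remove that shift.

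The second part concerns the match between design and analysis. Age is used to restrict randomisation but does not appear in the stated between-group comparison. If age is prognostic, leaving it out forgoes precision that the stratification was meant to secure.

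**Working it through.** **Inputs from the protocol (Sample size).** FJS-12 difference 17.7 points, effect size 0.61, power 80%, α 5% (two-sided assumed), dropout 20%, N = 110.

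**Reproducing N.** A two-sample t-test with d = 0.61 needs 43.2, so 44 per arm. Then 88 / (1 − 0.20) = 110, which matches. Stratification does not enter this formula.

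**Standard error of the contrast.** Implied SD = 17.7 / 0.61 = 29.0. With 44 per arm, SE = 29.0 × √(2/44) = 6.2 points.

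**Assumptions, not in the document.** Second centre recruits 30 of 110; 55 per arm overall; FJS-12 differs by 10 points between centres.

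**Chance imbalance, no blocking.** The number of the 30 second-centre patients allocated to SC+P is hypergeometric (110, 55, 30).
- SD = √(30 × 0.5 × 0.5 × 80/109) = 2.35
- 95% range: 10 to 20
- Probability of 20:10 or worse in either direction: 0.053

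**Shift in the contrast.** Shift = centre difference × (20/55 − 10/55) = centre difference × 0.182.

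| Assumed centre difference | Shift at a 20:10 split | Shift / SE |
|---|---|---|
| 5 points | 0.9 | 0.15 |
| 10 points | 1.8 | 0.29 |
| 15 points | 2.7 | 0.44 |

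At 10 points the shift is about a tenth of the 17.7-point target. A one-SD imbalance gives only 10 × (2 × 2.35/55) = 0.85 points.

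**Varying the centre share and the scheme.** Simulation with 110 patients, two equally likely age strata and the second centre joining later gives the 95th percentile of the absolute difference between arms in second-centre share, in percentage points. The three columns are age-only stratification, age and centre with blocks of 4 or closed balanced lists, and age and centre with neither.

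| Second-centre share | Age only | Age and centre, blocked or balanced | Age and centre, unrestricted |
|---|---|---|---|
| 20% | 11.6 to 14.7 | 2.9 to 3.6 | 15.0 |
| 30% | 15.3 to 17.2 | 0.7 to 3.3 | 17.3 |
| 50% | 18.2 to 20.0 | 0 to 3.6 | 18.3 |

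The mean difference is essentially zero throughout. With a 10-point centre difference, the 95th-percentile shift is about 1.2 to 2.0 points under age-only stratification, against 0 to 0.4 with blocked or balanced centre-specific lists. The last column shows that separate sequences without blocks or balanced lists gain nothing.

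**If the existing age-stratum lists are already blocked.** With blocks of 4 (assumed) and 30 second-centre patients, the 95% range depends on when the second centre joins. If the first centre recruits alone for 70 patients, the range is 12 to 18 and a 20:10 split or worse has a probability of about 0.3% or less. If the centres overlap from patient 31, the range is 11 to 19 and the probability about 4%.

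**The case against.** The strongest reply is that an unadjusted comparison of randomised arms is unbiased and its standard error already allows for chance imbalance in any baseline factor, centre included. That is correct. A reader might infer that centre is confounded with treatment, and the protocol does not support this: allocation is 1:1 at both sites, so centre is not systematically linked to arm.

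Other tempting readings also fail. Staged entry does not create imbalance, and with blocked lists it reduces it. Local assessors cannot move the primary outcomes, because FJS-12 and Mod-PEI-2 are self-completed paper questionnaires. Early postoperative rehabilitation follows a standardised protocol, and staff at both sites share training and monthly meetings. Nothing in the article says that the second centre will be the smaller one or that waiting times differ by site. The authors' remark on internal validity does not refer to allocation.

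It can also be said that a condensed article may leave block sizes, envelope handling and model terms to a fuller document. That is fair for block size and handling, and separate lists by centre may exist. But the article twice names its stratification factor, and no later analysis document can balance patients already allocated. It also names the between-group test, and that test has no place for covariates. The conditional adjustment list covers some routes by which a centre could act. However, its items arise after randomisation, whereas centre is a baseline factor for which adjustment is straightforward.

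**Conclusion.** The point holds in a limited form. Chance imbalance by centre is not controlled by the stated design, and the stated between-group tests include neither the factor used to stratify nor centre. This is a missed opportunity for balance and precision; it does not invalidate the comparison.

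The size is small. Under the assumed 30 of 110 split and 10-point centre difference, a roughly 1-in-20 allocation shifts the FJS-12 contrast by 1.8 points, about 0.3 SE. Across second-centre shares of 20% to 50%, the 95th-percentile shift is 1.2 to 2.0 points. It would rarely change a conclusion. Centre split, centre effect, age split and block size are all assumptions. The change is still worth making because it is inexpensive and the Trial status section expects recruitment to run through 2026. The limitations also note that the statistician is not blinded, so a centre adjustment chosen after seeing the data would be open to challenge.

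**What to change.** 1. **Allocation.** For the second centre, or for all remaining patients if it has already opened, have the independent person prepare permuted-block 1:1 sequences by centre within each age stratum. Conceal the block size from the trial coordinator, who performs the allocation. Patients already randomised keep their allocation. Amend the Randomisation section and the abstract to name centre and age, and give the date of the change. If centre-specific lists are already in use, one sentence saying so settles this part.

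2. **Analysis.** Replace the unadjusted between-group tests of the primary outcomes with a regression that includes treatment, age stratum and centre as prespecified fixed factors: linear for FJS-12, and linear or logistic for Mod-PEI-2 according to whether the score or the proportion above 21 is analysed. This also deals with most of the chance imbalance among patients already allocated.

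**Cost.** One further set of envelopes, a short amendment, and a change from a t-test to a model. There will be four smaller strata instead of two, some possibly ending in incomplete blocks. No extra patients or staff are needed, and N stays at 110.

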### Prehabilitation

Prehabilitation consists of 8 weeks of on-site, supervised and individualised exercise therapy together with patient education. It is delivered in a group format two times per week, at a fixed time in the afternoon (approximately 1 hour per session), by physiotherapists with experience in the rehabilitation of OA and TKR.

After the 8-week intervention, patients are advised to continue the exercise therapy either in supervised sessions or unsupervised at a location of their choice until the surgery date. Patients who choose to continue with unsupervised exercise therapy have check-ins scheduled by phone or video conference every other week with the physiotherapist in charge of the intervention to discuss exercise progression and adjustments.

Physiotherapists at the participating clinics are trained in the intervention’s content and structure two times before enrolling patients. They work with the trial coordinator to review these materials, and monthly meetings are held to monitor sessions, ensure treatment fidelity and address any issues.

